#### Level I

Patient characteristics: not responsive to commands.

Physical exercises: passive cycle ergometer for lower limbs (15-min duration) with 35 revolutions per min, passive upper limb mobilization with ten repetitions of flexion and abduction of shoulders and triple hip flexion, and tibialis ischial stretching and simultaneous functional electrical stimulation (FES) in the right and left quadriceps muscles. FES will be set with the following parameters: frequency (R) 60 Hz, pulse width (T) 250 ms, on time of 4 s and off time of 8 s, applied for 20 min.

Postural changes: passive transfer of decubitus.

#### Level II

Patient characteristics: responsive to commands, muscle strength (MS) less than three for hip flexors and extensors according to the Medical Research Council (MRC) Scale [32].

Physical exercises: assisted exercises of upper limbs (one series of ten repetitions), cycle ergometer preferentially assisted in the lower limbs with a duration of 15 min, FES in the quadriceps muscles (15-min duration), bridge exercise (one series of ten repetitions), video game session of 15-min duration.

Postural changes: active bed transfer, assisted bedside sitting, trunk control exercises, attempted orthostatism, and assisted walking with specific technologies.

#### Level III

Patient characteristics: responsive to commands, MS greater than or equal to three for hip flexors and knee extensors according to the MRC Scale.

Physical exercises: resistive exercise of shoulder abductor, elbow flexor, hip flexor, and knee extensor muscles (one series of ten repetitions with a load of 0.5 kg), active cycle ergometer in lower limbs (15-min duration), bridge exercise (one set of ten repetitions), video game session lasting 5 min.

Postural changes: active transfer to a seated position at bedside, sit and lift training (ten repetitions), orthostatism and walking with or without assistance for a distance less than 20 m, sitting in an armchair.

#### Level IV

Patient characteristics: responsive to commands, MS greater than three according to the MRC Scale, completion of level III of the program.

Physical exercises: continuation of resisted exercises (two sets of ten repetitions with a 0.5-kg load), bridge exercise (one set of ten repetitions), video game session for 5 min.

Postural changes: actively sitting at the bedside, orthostatism and walking with or without assistance for a distance greater than 20 m, training in going up and down steps, sitting in an armchair.

#### Level V

Patient characteristics: responsive to commands, MS greater than three according to the Medical Research Council (MRC) Scale, completion of level IV of the program.

Physical exercises: continuing resisted exercises of upper and lower limbs (one series of ten repetitions with a load of 1.0 kg), bridge exercise (one series of ten repetitions), video game session lasting 5 min.

Postural changes: independent maintenance of bedside sitting, active orthostatism, and independent walking with or without aid for a distance greater than 20 m, climbing stairs, and sitting in an armchair.

#### Choice of activity level and criteria for progression in the mobilization program

The program consists of different levels of mobilization with progressive levels of activity, intensity, and types of exercise. To determine the appropriate level, the methods used to determine the appropriate level for each patient will be the patient’s ability to understand and their MS. The patient’s capacity to understand will be evaluated through requests to follow simple commands, such as “Put your hand on your head, bend your legs, open and close your eyes.” MS at the beginning of the program will be assessed using the MRC Strength Scale. A score of 3 points will be used as a cut-off to determine whether the patient can perform the movement alone and against the action of gravity. Patients capable of these movements will progress to the next level.

Thus, if a patient meets the criteria to enter the program, the next step will be to determine the activity level at which he or she will start the protocol. The first criterion is whether the patient can respond to commands; patients who are unresponsive will enter the program at level I. Patients who can follow commands will begin at levels II, III, IV, or V. To determine the specific level of each patient, MS is measured, with a cut-off score of 3 on the force scale. Patients with MS less than 3 will begins the program at level II, patients with MS of 3 or greater will begin at level III. The difference between level I and the other levels is the ability to understand commands, and the differences between the other levels depend on MS. After completing a level, the patient can move to the next level.

Patients will be reassessed daily to determine whether they can advance to the next level. To progress from level I to level II, the patient should have improved consciousness and be able to respond to commands. If MS is less than 3, the patient will enter level II. If the patient’s MS is equal to or greater than 3, they can advance directly to level III.

From level II onwards, patients can advance by one level when they can perform all the exercises prescribed for that level. Therefore, at levels III, IV, and V in the early and progressive mobilization program, the patient must be able to perform all of the physical exercises and postural changes at their present level or they will remain at the same level for the following day. When patients can complete all of the activities, they advance to the next level on the following day.

Patients in both the control and intervention groups will be monitored throughout the therapy for hemodynamic and respiratory stability. Therapy will be discontinued if the RR is above 35 breaths/min, the MAP is below 60 mmHg or above 120 mmHg, the HR is below 60 bpm or above 140 bpm, or the patient experiences discomfort or unrelenting pain during the therapy.

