### Participants

Participants will be patients admitted to the ICU who are 18 years old or older with a Barthel Index equal to 100 points before hospitalization, who have not been transferred from another hospital, and who meet the criteria for inclusion in the progressive mobilization program will be enrolled in the study. The criteria for for initiation and continuity the progressive mobilization program follow the safety consensus described in the academic literature [19] and some points are as follows: respiratory rate (RR) ≤ 35 breaths per min, absence of cardiac arrhythmias or acute ischemia, heart rate (HR) between 50 and 140 beats per min, without the use of vasoactive drugs or without dose increase, mean arterial pressure (MAP) between 60 and 120 mmHg, absence of active bleeding, and no prescription of bed rest. Patients with MV with inspired fraction of inspired oxygen (FiO_2_) ≤ 60% and positive end-expiratory pressure (PEEP) ≤ 10 cmH_2_O are also eligible to participate.

Patients to be excluded include patients with neurological diagnoses associated with motor alterations, who refuse to carry out the proposed exercises or ask to withdraw less than 3 days after beginning the protocol, with contraindications for movement, those with pre-existing amputations or who undergo amputation upon hospitalization, and those who die before the final evaluation will be excluded from the study.

After admission to the ICU, patients will be evaluated at all times of the day regarding the inclusion criteria in the program. Patients will be evaluated within 2 days of admission to the ICU to participate in the study. If they do not present the criteria for initiating a mobilization program in that period [19], they will not be randomized and will not be included in the study.

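### The lower heart-rate limit for starting and continuing mobilisation (50 beats/min) contradicts the lower limit for stopping therapy (60 beats/min), so 50–59 beats/min falls under both rules

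*Protocol article*

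**What the plan says.** Two sections of the protocol article set limits on vital signs for mobilisation.

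- **Participants.** The listed criteria are described as those "for initiation and continuity the progressive mobilization program follow the safety consensus described in the academic literature", so they cover carrying on with the programme as well as entering it. They include "respiratory rate (RR) ≤ 35 breaths per min", "heart rate (HR) between 50 and 140 beats per min" and "mean arterial pressure (MAP) between 60 and 120 mmHg".
- **Choice of activity level and criteria for progression.** The monitoring rule applies to both arms: "Patients in both the control and intervention groups will be monitored throughout the therapy for hemodynamic and respiratory stability". The stopping limits follow: "Therapy will be discontinued if the RR is above 35 breaths/min", "the MAP is below 60 mmHg or above 120 mmHg", and "the HR is below 60 bpm or above 140 bpm". Discomfort or persistent pain is a further reason to stop.

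The stopping rule has no grace period, no condition on change from the resting value, and no exemption for a patient who was already below 60 when the session began.

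**The concern.** One section allows mobilisation to begin and go on at a heart rate of, say, 55 beats/min. The other requires therapy to stop at that same rate. Both are stated as operative rules, so whoever is at the bedside has no way to comply with both.

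Two things are at stake. The first is safety conduct: a threshold that decides whether a critically ill patient is exercised should have one meaning. The second is consistency of the delivered treatment. The stopping rule covers both arms, but the arms are treated by different staff. A dedicated physiotherapist delivers the research programme (Intervention group section), and the unit physiotherapists treat the controls at their own discretion (Control group section). Sessions cut short or carried on according to different readings would alter the amount of mobilisation delivered and the measured activity level, which is a secondary outcome. Recruitment has been under way since February 2017, so sessions may already have been handled under either reading.

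**Working it through.** There is no published figure to reproduce. The check compares the stated limits.

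| Variable | Start/continue (Participants) | Stop (Choice of activity level) | Values meeting both rules |
|---|---|---|---|
| Respiratory rate, breaths/min | ≤ 35 | > 35 | none |
| Mean arterial pressure, mmHg | 60 to 120 | < 60 or > 120 | none |
| Heart rate, upper limit, beats/min | ≤ 140 | > 140 | none |
| Heart rate, lower limit, beats/min | ≥ 50 | < 60 | 50 to 59 |

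1. The two rules are compatible for a variable when no value lies both in the permitted range and in the stopping region.
2. For respiratory rate, mean arterial pressure and the upper heart-rate limit, the stopping region begins exactly where the permitted range ends. The overlap is empty.
3. For the lower heart-rate limit, the overlap is the set with 50 ≤ HR < 60. In whole beats/min that is 50, 51, …, 59, or 59 − 50 + 1 = 10 values.
4. Could the lower value be only a screening limit, with a separate limit inside the session? The Participants criteria are stated for continuity as well as initiation, so the text does not confine them to screening. Even if it did, a patient cleared to begin at 50–59 would meet the stopping rule while the rate stayed there.
5. How many patients does this touch? That would need the distribution of heart rate in this unit at screening and at each session. The document gives neither, so no count is calculated.

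**The case against.** The strongest reply is that the two sections govern different things: one the programme, the other an individual session under monitoring. A stricter limit during exercise could then be intended. The difference in wording is real, and matching limits elsewhere make a slip likely without proving one. What the documents support is that the two limits are unreconciled. They do not show which value was intended, or that either is a printing error. The reply still does not remove the conflict, because the Participants criteria expressly extend to continuity.

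A reader might also infer that patients in this band would be randomised and then have every session stopped, or might put a number on such patients. The documents do not support that. Eligibility is assessed within 2 days of admission, while the stopping rule is applied during sessions held twice daily over a stay averaging 12 days. Heart rate varies over that time and may rise with activity. The conflict exists only while the rate is at 50–59, and any patient count would need assumptions both about how common that is and about how long it lasts.

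A third inference would be a biased adverse-event comparison. The outcomes section records respiratory or haemodynamic instability related to motor therapy, but it does not say that a session stopped for a heart rate below 60 counts as such an event. The stopping rule is also the same for both arms. Inconsistent classification is possible; differential bias is not shown.

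It is also fair to say that randomisation, the primary endpoints (Barthel Index and ICU Mobility Scale), the sample size and the planned comparison are untouched.

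The article being a condensed account does not help here. The Participants section says that it lists only some of the criteria, but heart rate is among those listed. Two printed numbers conflict, and further detail elsewhere could not make both hold as they stand.

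**Conclusion.** The point stands as an internal contradiction in an operative safety threshold. Between 50 and 59 beats/min, at the start of or during a session, the document tells staff both to proceed and to stop. Every other numerical limit shared by the two sections agrees, and no explanation is offered for this one.

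Its established size is the 10-beat band and nothing more. The number of patients or sessions affected is unknown, and the effect on the primary outcome is probably small. The case for correcting it rests on patient safety and on uniform delivery of sessions. It assumes only that both rules are meant to be followed as printed. Which lower limit is appropriate is a clinical question and is not judged here.

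**What to change.** - The clinical investigators should reconcile the Participants section with the section on choice of activity level and progression, so that the lower heart-rate limits for initiation, continuation and discontinuation do not contradict each other. If different limits for different stages are intended, the text should say so and state what applies to a patient who lies between them.
- The reconciled monitoring limit should go to the physiotherapists treating both arms. The unit physiotherapists should receive the limit alone, because the Control group section withholds the intervention protocol from them.
- If heart rates during sessions were recorded, sessions in the 50–59 band should be classified by one consistent rule when adverse events are tabulated. The article does not say that session heart rates are kept, so this step depends on what was stored.

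The cost is a short amendment and a notice to staff. Classifying past sessions is extra work, and is possible only if the data exist.

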#### Patient assessment procedures

At the time of admission to the ICU and up to 2 days after admission, the patient will be examined against the inclusion criteria. The patient’s functionality in the 2 weeks before admission will be evaluated with the Barthel Index, which will be assessed by directly questioning the patient or their caregiver if they are unable to respond. Evaluation will include hemodynamic, respiratory, and cardiac stability for the safe practice of early mobility, and the absence of exclusion criteria will also be assessed. The patient will then be randomly placed in the control group or the intervention group.

After the patient is enrolled in the study, the initial variables will be collected, consisting of data related to the patient and their hospitalized and pre-hospitalization levels of functionality. At that time, an accelerometer will be placed on the patient to monitor their level of physical activity during the entire stay in the ICU.

Data on the patient’s hospitalization and the evolution of their condition, as well as the level of physical activity performed, will be collected during the entire stay in the hospital.

Upon discharge from the ICU or within 2 days of discharge, all patients will undergo a complete evaluation of their respiratory, muscular, and functional systems through methods already described in the academic literature and performed by a blind evaluator. The accelerometer will be removed, and the data will be analyzed in a dedicated computer program. Figure 2 shows a flowchart presenting the methods used in the study.

**Fig. 2 Fig2:**
[figure not shown]
Flowchart of the study

Patients in both groups will use an Actigraph wGT3X-BT accelerometer (ActiGraph LLC®, Pensacola, FL, USA) throughout the length of their hospital stay, a tool which analyzes their position and level of activity. The accelerometer will be placed on the dominant lower limb using a bandage and will not be removed until discharge, allowing information on the patient’s physical activity to be collected objectively. The evaluation of the intensity of the exercises performed during ICU stay in both groups will be performed through the parameters evaluated by the accelerometer. This instrument is able to identify the intensity of the exercise performed, and for analysis we will divide it into mild, moderate and intense or absence of activity. Exercise intensity will also be monitored and evaluated by the Borg Scale at the end of each physical therapy session. At the end of the ICU stay, the equipment will provide data such as the exercise intensity and time spent lying down, sitting, and standing [24].

The following data concerning hospitalization will be collected: use of vasoactive drugs, use of corticoids or neuromuscular blockers, hypoglycemia, the presence of sepsis, surgery, hemodialysis, use of invasive and non-invasive MV, tracheostomy, and the number of days spent in the different therapies that were evaluated.

Evaluation of the respiratory system, muscular system, and functionality after ICU discharge will be performed by a blind evaluator using methods previously described in the academic literature. These data will be correlated with the physical activity data obtained from the accelerometer.

The respiratory evaluation will be performed using the maximal inspiratory pressure test with the use of a manovacuometer (Wika Corporate®, Klingenberg, Germany), while evaluation of pulmonary function will be done through spirometry, assessing the forced expiratory volume in 1 second (FEV_1_) and maximum voluntary ventilation [25] with a Datospir – Micro C digital spirometer (Sibelmed®, Barcelona, Spain).

The muscular evaluation will be performed by measuring MS with a handgrip dynamometer (Jamar Enterprises LDT®, Hoddesdon, United Kingdom) [26]. Muscle activity will be measured by electromyography of three muscles in the lower limbs—the anterior tibial, medial gastrocnemius, and vastus lateralis muscles—using a Miotool Miotec device (Miotec Equipamentos Biomédicos Ltda®, Porto Alegre, Brazil). The patient will perform the voluntary contraction three times in each muscle, accompanied by an electrogoniometer (Miotec Equipamentos Biomédicos Ltda®, Porto Alegre, Brazil) [27, 28].

Muscular function and mobility will be evaluated using the Timed Up and Go test [29] and the 2-Minute Walk test [30].

Functionality will be evaluated using the Barthel Index [31], measured by directly questioning the patient and by using the ICU Mobility Scale (IMS) [32].

The demographic data and initial evaluation of the patient will be collected on a data sheet. The patient’s physical activity data will be collected by the accelerometer and stored in the equipment’s software, and will later be included in the general tabulation of patient data. The physical evaluation data (dynamometry, electromyography, respiratory MS, and spirometry) will be collected on the same data sheet.

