#### Control group

The control group will perform the conventional treatment offered by the unit physiotherapists. The unit physiotherapist will not have access to the protocol and equipment used, and the exercises that patients perform will be at the physiotherapist’s discretion. Conventional therapy consists of passive, active assisted, and active mobilization as well as bed positioning, bedside and armchair transfers, orthostatism, and ambulation; however, the type of therapy will not be defined in advance, but instead will be at the discretion of the attending physiotherapist and without a pre-established routine. No technological equipment will be used for this group, as these elements are not part of the normal service.

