### Primary and secondary outcome measures and assessment points

The outcome variables of the study will be respiratory, muscular, and functional variables; the length of stay in the ICU; and analyzed variables of physical activity, measured by the accelerometer.

The primary outcome will be the functional status at discharge from the ICU. The functional status is the difference between baseline and final score on both the Barthel Index and the IMS. Therefore, at discharge from the ICU, the Barthel Index and IMS will be redone, and the quantitative final score on those scales will be considered as the primary endpoints of the study. The secondary outcomes will be the respiratory and muscular variables and the number of days of hospitalization in the ICU. Further secondary outcomes will be the variables of physical activity performed during this period, which include an analysis of the intensity levels of the exercise to which the patient was submitted and the percentage of time spent sitting, lying, and standing.

For both groups, the occurrence of any adverse events related to motor therapy, such as respiratory or hemodynamic instability, accidental removal of invasive devices, falls, or pain will be recorded. Figure 3 illustrates the schedule of enrollment, allocation, intervention, and assessment of the study.

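### The leg-worn accelerometer has no category for imposed movement, and device-driven leg movement is given only in the intervention arm, so part of an activity-intensity difference may be prescription rather than patient activity

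*Protocol article*

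**What the plan says.** **Measurement.** Under Patient assessment procedures, both arms wear the accelerometer on the leg: "The accelerometer will be placed on the dominant lower limb using a bandage and will not be removed until discharge". It therefore runs during therapy. The "intensity of the exercises performed during ICU stay in both groups will be performed through the parameters evaluated by the accelerometer", and for analysis "we will divide it into mild, moderate and intense or absence of activity". The Borg Scale after each session is the only other intensity measure named.

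**Role.** The outcome section states: "Further secondary outcomes will be the variables of physical activity performed during this period". The hypothesis at the end of the Background has two parts, and higher activity in the ICU is one of them. The accelerometer data are also to be correlated with the respiratory, muscular and functional results.

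**Treatment.** Level I is for patients who do not respond to commands. It prescribes "passive cycle ergometer for lower limbs (15-min duration) with 35 revolutions per min" and 20 minutes of stimulation to both quadriceps. Level II prescribes 15 minutes of preferentially assisted cycling and 15 minutes of stimulation. From level III the cycling is active. For controls, "No technological equipment will be used for this group", but the same section lists passive and active-assisted mobilization as part of conventional therapy, at the physiotherapist's discretion.

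**Wear period.** One paragraph has the device fitted "to monitor their level of physical activity during the entire stay in the ICU", while the text after Figure 2 has it worn "throughout the length of their hospital stay".

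**The concern.** The instrument that compares the arms on activity is attached to the limb that the intervention equipment moves. An accelerometer responds to motion whatever its source, and the planned categories leave imposed motion nowhere to go except into an intensity class, or into absence of activity if it falls below an unstated threshold. The device-driven share occurs in one arm by design.

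Two results are at stake. An activity advantage could arise partly from the prescription even if no patient moved more of their own accord, yet the Discussion expects higher activity to lead on to better function. The planned correlations are also exposed. Imposed movement is concentrated in unresponsive or very weak patients, so it adds recorded activity where function is likely to be low.

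**Working it through.** The plan gives no figure for this point, so there is none to reproduce. The check sets the stated procedures against each other and works out the size of the imposed dose.

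**1. Is imposed movement inside the record?** The sensor is not removed for therapy, and intensity is taken over the ICU stay. Nothing in the article flags or sets aside cycling or stimulation periods. Treatment exposure is collected as days in each therapy, which cannot locate a 15-minute window. An unresponsive patient cannot give a Borg rating, so at level I the sensor is the only usable intensity measure.

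**2. Is it unequal between arms?** Both arms have conventional physiotherapy in the morning. The arms differ in the afternoon: the research protocol in one, a second conventional session in the other. Cycle and stimulator movement therefore falls in the intervention arm alone. Manual passive movement can occur in both arms, in unstated amounts. The net imbalance cannot be derived.

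**3. Dose per session** (inputs from Levels I and II)
- Level I cycle: 35 rev/min × 15 min = 525 revolutions.
- Level I stimulation: 4 s on + 8 s off = 12 s per cycle; 20 × 60 / 12 = 100 stimulations, 100 × 4 = 400 s on.
- Level II stimulation, assuming the same timing: 15 × 60 / 12 = 75 stimulations, 300 s on.
- Share of a 24 h record: 15 / 1440 = 1.0% for the cycle; (15 + 20) / 1440 = 2.4% if stimulation follows the cycle.

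Stimulation may displace the limb little. The cycle alone carries the argument.

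**4. Relative to active time.** No baseline is given. Assuming 10, 30, 60 or 120 min/day of otherwise detectable activity, 15 minutes adds 15/10 = 150%, 15/30 = 50%, 15/60 = 25% or 15/120 = 12.5%. These figures apply to one patient-day at level I, or to level II if the assisted cycling is wholly imposed. They are not arm means.

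**5. What a net shift could do to the test (illustration only).** Take 48 per arm, no true difference in voluntary activity, active minutes per day compared at two-sided 5%, and the SD assumed. The chance of a significant result favouring the intervention is Φ[(shift/SD) × √(48/2) − 1.96], with √24 = 4.899. For a shift of 15 and SD 30: 0.5 × 4.899 − 1.96 = 0.489, giving 0.69. With no shift the chance would be 0.025.

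| Mean net shift, min/day | SD 15 | SD 30 | SD 60 |
|---|---|---|---|
| 15 (all intervention patient-days affected) | 0.998 | 0.69 | 0.23 |
| 7.5 (half affected) | 0.69 | 0.23 | 0.09 |
| 3.75 (a quarter affected) | 0.23 | 0.09 | 0.05 |

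The table assumes that every cycling minute is classed as active, ignores the extra spread when only some days are affected, and takes the shift as net of manual passive movement in controls. The article supplies neither the share of days at levels I and II nor the SD, so the table shows sensitivity and is not an estimate.

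**6. Wear period.** Intensity is defined over the ICU stay, and the device comes off with the evaluation at ICU discharge or within 2 days of it. The hospital-stay wording disagrees with this.

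**The case against.** The strongest reply is that the outcome is not defined as voluntary movement. The outcome section describes the intensity of exercise that the patient was put through, and passive cycling fits that description. This stands as a possible reading. On it, however, an advantage at level I partly restates what was prescribed and does not show more active patients. The article should say which quantity it means.

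A reader might infer that imposed movement is counted in the intervention arm only. The documents do not support that: controls may have passive and active-assisted mobilization, and the sensor records it too. Only the cycle- and stimulator-driven part is confined to one arm. It follows that excluding device minutes alone would be unfair to the intervention, since manual movement would still count for controls.

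A reader might also infer that ward days dilute the comparison. That has little support, because intensity is taken over the ICU stay and the device is removed at or near ICU discharge. What remains is wording to reconcile.

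Finally, accelerometer processing is often left to an analysis plan, and the thresholds are not visible here. That is fair for thresholds and wear-day rules. But this article itself fixes the leg site, uninterrupted wear and the four categories, and session times that were never logged cannot be cleanly recovered by a later plan.

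**Conclusion.** The point holds as a limited, inexpensive improvement. As written, the plan can count device-imposed leg movement as activity in a comparison that serves half of the hypothesis, and in the correlations with function. The known size is 15 minutes, or 525 revolutions, per level I session. The relative inflation is unknown: the percentages and error rates above depend on assumed baselines, SDs and shares of affected days, and should not be read as the bias in this trial.

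The effect is confined to days at levels I and II, and at level II part of the cycling may be the patient's own effort. The time lying, sitting and standing is much less affected. The primary Barthel and ICU Mobility Scale endpoints are not affected. The conclusion rests on two inferences: that passive mode means motor-driven, drawn from the ergometer's description and the set speed in unresponsive patients, and that the software registers such cycling as activity.

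**What to change.** - In both arms, record start and stop times of all passive or assisted leg movement, whether by cycle, stimulator or hand.
- Class those minutes as a separate passive/assisted category. Make the between-arm intensity comparison and the correlations on the remaining activity, and report totals including imposed movement alongside, labelled as exercise delivered.
- For patients treated before logging begins, report total movement only, or add a sensitivity analysis where session times can be recovered.
- Align the hospital-stay wording after Figure 2 with the ICU-stay window used elsewhere under Patient assessment procedures.

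The cost is one extra line on the session sheet in both arms and one classification step in the analysis. Some patient effort in assisted level II cycling will leave the main comparison, and the reported activity advantage may shrink. Treatment does not change.
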